**Methods/design:**

A baseline survey of 2314 randomly selected 18- to 24-year-old sexually active men and women has been conducted. The WC and mass media will be introduced throughout 40 urban wards in and surrounding Lusaka, Zambia. The baseline survey will serve as a quasi-control arm to determine the impact of introducing the WC with mass media. Half of the wards will be randomly allocated to additionally receive the IPC intervention. A single-blind randomized controlled trial will determine the impact of the IPC intervention on knowledge, uptake, and use of the WC. After one year, another 2314 individuals will be randomly selected to participate in the endline survey.

We hypothesize that (1) the distribution and media campaign of the WC will increase overall condom use in selected urban wards, and specifically use of the WC; (2) the IPC intervention will significantly impact knowledge, acceptability, and use of the WC.

The primary outcome measures are use of the WC, use of any condom, and willingness to use the WC. Secondary outcomes include measures of knowledge, acceptability, and choice of contraception.

Odds ratios will be estimated to measure the effect of the intervention on the outcomes with 95% confidence intervals. All analyses will be based on the intention-to-treat principle.

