**Fig. 1 Fig1:**
[figure not shown]
Summary of conceptual framework

The primary objectives of this evaluation are:To assess the effect of the introduction of the WC on the overall condom market (self-reported condom use and self-reported use of WC)To determine the additional effect of an IPC intervention on self-reported *use of the WC* as compared with just mass media including a website (controlling for any differences between the intervention and control groups)To determine the additional effect of an IPC intervention on self-reported *use of any condom* as compared with just mass media including a website (controlling for any differences between the intervention and control groups)To determine the additional effect of an IPC intervention on *willingness to use an FC* (and specifically, the WC) as compared with just mass media including a website (controlling for any differences between the intervention and control groups)

The secondary objectives of this evaluation are:5.To determine the effect of an IPC intervention on self-reported *knowledge, attitudes, and practices regarding the FC, specifically the WC*, as compared with just mass media including a website (controlling for any differences between the intervention and control groups)6.To determine the effect of an IPC intervention on community-level *acceptability of an FC, specifically the WC*, compared with just mass media including a website (controlling for any differences between the intervention and control groups)7.To determine the effect of an IPC intervention on self-reported *changes in interpersonal communication with sexual partners* regarding contraceptive use as compared with just mass media including a website (controlling for any differences between the intervention and control groups)8.To assess women’s and men’s preferences for condom brands.

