## Methods/design

The overall aim of this study is to assess the impact of introducing the WC on the overall condom market. We will also evaluate the effectiveness of IPC plus mass media plus distribution of WC (intervention) compared with mass media plus distribution of WC (control) on the self-reported prevalence of WC use and prevalence of overall condom use using an RCT design. Forty urban wards in Lusaka and nearby districts (Chilanga, Kafue, and Chongwe) will be randomized to the control or intervention arm with a 1:1 allocation ratio. The baseline survey conducted in all 40 wards will be analyzed as a quasi-control arm in order to assess the effect of the introduction of the WC on the total condom market. This will be done for two reasons: (1) there are no comparably urban areas in the country to act as control settings; (2) the potential for spillover for a new condom product and its marketing campaign is extremely high, making a true control arm logistically and technically impossible. The media campaign will be displayed on a website and billboards throughout the city; thus these cannot be geographically limited.

When the baseline survey is implemented, no WC will be available, as is the status quo in Lusaka. After rollout of the WC, wards in the control arm will receive only the WC and a mass media campaign. Intervention wards will receive the WC, a mass media campaign, and the IPC intervention. The RCT component of this study will aim to evaluate the added impact of the IPC intervention compared with just distribution of the WC and the mass media campaign. The trial will be evaluated through baseline and endline questionnaires administered to eligible individuals residing within randomly selected households located in these wards. The Standard Protocol Items: Recommendations for Interventional Trials (SPIRIT) checklist was used to prepare the study protocol (Additional file 1). The resulting protocol schedule of procedures and activities for this study is outlined in Table 1 as per the SPIRIT guidelines.

**Table 1 Tab1:** SPIRIT protocol schedule of procedures and activities for Maximum Diva study

	Study period					
	Prep. phase	Baseline survey	Randomization	Intervention period	Endline survey	Close-out
Activity	*-t* _*1*_	0		*t* _*1*_	*t2*	*t3*
Enrollment:						
Sampling and mapping	X					
Informed consent written	X					
Hiring and training surveyors	X					
Piloting, revising survey tool	X					
Interventions:						
Randomization			X			

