A structured questionnaire was administered to each eligible and consented individual who met the inclusion criteria. Survey interviewers were either male or female and work for Innovations for Poverty Action (IPA) Zambia. Each interview lasted about one hour and took place in the home but away from other household members, in private. The questionnaire collects socio-demographic information, information regarding condom use, sexual behavior, knowledge and beliefs specifically regarding condoms, contraceptive options, and communication with sexual partners. A small reimbursement amount was provided to participants who completed the survey. The study enrolled both men and women.

After the baseline survey was completed in January 2016, all 40 wards were randomized to receive the control (WC plus mass media) or intervention (WC plus mass media plus IPC), and were allocated by an IPA statistician using a Stata program. Ward level population density based on the 2010 census data, ward level poverty, and average distance to the nearest health facility were used to stratify the randomization. Additional balance checks were conducted to ensure randomization was successful. Each ward has been mapped including the IPC sites, and all visited houses enumerated and given an ID. Since randomization, the IPC intervention has been implemented in intervention wards only. Only the IPA statistician and the implementing partner (the SFH) know the allocation of wards. The endline survey is planned for March 2017, and will follow the same protocol as outlined above for the baseline survey. The endline survey will have additional questions regarding exposure to the mass media and IPC intervention, including pictures to prompt recall. Households will be randomly selected for both surveys; the same households will not be approached.

The Consolidated Standards of Reporting Trials (CONSORT) randomization and survey structure are described in Fig. 3.

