### Primary and secondary outcomes

The primary and secondary outcomes listed below correspond to the primary and secondary objectives.

The primary outcomes are:Increase in the *prevalence (percentage) of WC* (self-reported) use among men and women aged 18–24 years evereverlast 6 months,most recent sexual intercourse.

2.Increase in the *prevalence (percentage) of any condom* (self-reported) use among men and women aged 18–24 yearseverin the past 6 months at most recent sexual intercourse.

3.Increase in the *willingness to use* the WC in the future among men and women aged 18–24 years.

The secondary outcomes are:4.Self-reported increase in knowledge, improved attitudes, and practices of both male and female condoms after attending IPC intervention5.Self-reported increase in acceptability (community awareness) of FCs6.Self-reported improvement in communication with sexual partner(s) regarding use of male and/or female condoms for STI prevention and/or family planning7.Self-reported condom brand preference before and after rollout of the WC.

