For the RCT component of the study, we will analyze the impact of the IPC intervention on our outcomes of interest (male condom use, WC use, willingness to use the WC), comparing intervention to control wards. Analyses will be conducted in Stata v12 (StataCorp, College Station, TX, USA). Results will be adjusted for any ward level clustering if it is identified. Multivariate regression analyses will be carried out to determine the impact of the IPC intervention on condom use (male condom and WC), controlling for demographic characteristics of participants.

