#### Statistical methods

For the primary and secondary outcomes we will estimate odds ratios with 95% confidence intervals. We will calculate the rates of self-reported contraception use per ward and willingness to use the WC. Descriptive analyses will be conducted, and several regression models will be run to determine the impact of IPC on each outcome variable of interest. All regression models will control for baseline characteristics of relevance to the outcome (either as potential confounders or as explanatory factors). Backward elimination methods will be used to remove non-statistically significant factors that do not improve the fit of the model and do not confound other associations observed. Multilevel models may be implemented to control for individual and ward level correlation, as individuals are nested within wards.

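### Secondary outcome 4 is defined by attendance at IPC, a post-randomisation event with no control-arm counterpart, and so does not match objective 5 or the intention-to-treat statement

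*Protocol article*

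**What the plan says.** Under Primary and secondary outcomes, item 4 reads "Self-reported increase in knowledge, improved attitudes, and practices of both male and female condoms after attending IPC intervention". The same section introduces the list with "The primary and secondary outcomes listed below correspond to the primary and secondary objectives".

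The matching objective is number 5 under Objectives and hypothesis. It asks for the effect of IPC on "knowledge, attitudes, and practices regarding the FC, specifically the WC*, as compared with just mass media including a website", with no mention of attendance.

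On delivery, Survey and randomization states "Since randomization, the IPC intervention has been implemented in intervention wards only", and Methods/design states that "wards in the control arm will receive only the WC and a mass media campaign".

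On analysis, the Abstract (Methods/design) states "All analyses will be based on the intention-to-treat principle". The Data management and analysis plan describes the trial analysis as "comparing intervention to control wards", and Statistical methods adds "For the primary and secondary outcomes we will estimate odds ratios with 95% confidence intervals".

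**The concern.** An outcome used to compare randomised arms has to be defined for everyone in both arms. Item 4 is defined by reference to an event that, by design, can occur in one arm only. That event is also a choice made after randomisation. According to the Intervention section, agents recruit at high-traffic points and through their own contacts, and Process evaluation treats take-up as something to be measured. People who end up in a session are likely to differ from those who do not in how reachable, interested or sexually active they are.

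What is at stake is the answer to objective 5. Anyone who takes the outcome line at face value would look at attendees, and the result would no longer be protected by the randomisation of wards. The data for such an analysis will exist, because Table 1 lists IPC attendance among the endline items and the endline questionnaire adds questions on IPC exposure.

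**Working it through.** No figure in the article is at issue, so the check sets the passages side by side and then shows in symbols what the wording would do.

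**1. Objective against outcome.** Objective 5 contrasts IPC with mass media only, among people in the wards. Item 4 refers to people after they have attended. The article says the two lists correspond, but on this item they do not. No other primary or secondary outcome carries an attendance condition, so item 4 departs from the article's own pattern.

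**2. Outcome against control condition.** IPC runs in intervention wards only, and control wards receive the product and mass media. A control-ward resident could attend only by crossing a ward boundary, which would be contamination and not the control condition. The phrase therefore defines no control-arm quantity from which the planned odds ratio could be formed.

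**3. Outcome against analysis principle.** Intention-to-treat and the ward comparison both classify respondents by the allocation of their ward. Attendance classifies them by later behaviour.

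**4. What following the wording would estimate.** Let *p* be the share of intervention-ward respondents who attend. Let *a* and *b* be the mean scores that would-be attendees and non-attendees would have without IPC, and *d* the effect of attending. Assume, for simplicity, that IPC does not affect non-attendees. By randomisation, the expected control-ward mean is p·a + (1 − p)·b.

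- Attendees against all control respondents: (a + d) − [p·a + (1 − p)·b] = d + (1 − p)(a − b).
- Attendees against non-attendees within intervention wards: (a + d) − b = d + (a − b).
- All respondents by ward allocation: [p(a + d) + (1 − p)b] − [p·a + (1 − p)·b] = p·d.

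The first two contain a selection term that is non-zero even when d = 0, unless attendees and non-attendees would have scored alike. The third contains none. These are differences in means; the planned odds ratio is on another scale but has the same problem.

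**5. Can the size be given?** No. The article states neither *p* nor *a − b*. Any number would only return the values assumed for them.

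**6. Is the sound version feasible?** Yes. The endline survey follows the same procedure as the baseline in all 40 wards, and the questionnaire covers knowledge and beliefs about condoms. Table 1 lists knowledge of the WC and IPC attendance as separate endline items, so nothing suggests that knowledge is collected from attendees only. Table 1 does not list knowledge of the WC among the baseline outcomes, and the WC was not available then. A ward baseline mean is therefore not documented for WC-specific knowledge.

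**The case against.** The strongest reply is that this is loose wording. Every passage that sets the comparison is based on allocation: objective 5, the description of the arms, the ward-level analysis and the intention-to-treat statement. The outcome list is itself said to follow the objectives. On that reading, the phrase is shorthand for the period after the IPC programme.

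Much of this stands. A reader might infer that the trial plans to compare self-selected attendees with everyone else, or that knowledge cannot be measured in control wards. The article supports neither. No passage restricts an analysis set to attendees, and knowledge is an endline item in its own right. Only the attendance qualifier lacks a control-ward counterpart. The reply does not rescue the definition, however, because the words have to be disregarded to obtain the analysis that the rest of the article describes.

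A reader might also extend the point to items 5 and 6, taking self-reported increase or improvement to mean retrospective self-ratings of change, since different households are surveyed each time. The article does not support that either. Neither item has an attendance condition. The primary outcomes are also headed as increases, and for condom use these are changes in prevalence between surveys. No question asking respondents to rate their own change is described.

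**Conclusion.** The point holds for item 4 alone. Its definition contradicts objective 5, the intention-to-treat statement and the ward-level comparison, and it has no control-arm counterpart. The conflict is in the outcome wording; a breach of intention-to-treat would arise only if the analysis followed that wording. In that case the result would combine the IPC effect with self-selection of unknown size. The conclusion rests on the text and on one inference, that attendance is voluntary, which the recruitment and take-up descriptions support. The primary outcomes are not affected. The line should be corrected before endline analysis.

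**What to change.** Delete the attendance condition from item 4. Define it as the level of knowledge, attitudes and practices at endline in all respondents, compared by the allocation of their ward. Adjust for the ward baseline mean only for items also asked at baseline; for WC-specific knowledge, compare endline levels without that adjustment. Label any analysis by IPC attendance as exploratory and keep it apart from the answer to objective 5. The same edit could settle a small difference in scope, since item 4 covers male and female condoms while objective 5 concerns the female condom and the WC in particular.

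The cost is rewording one line. The article describes a questionnaire that already covers this content, so no new data collection or change of sample size is needed.

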### Process evaluation

The RCT will be complemented by a process evaluation that is being conducted between the baseline and endline data collections. After the baseline survey was conducted, the intervention was rolled out: the WC is now be available throughout Lusaka coupled with the mass media campaign. The IPC intervention is being implemented in the randomly selected intervention wards. Since completion of baseline, IPA and SFH have been carrying out a process evaluation to assess the fidelity of the various components of the WC project as well as penetration of the IPC intervention. This is being done to assess the following: (1) availability and distribution of the WC, (2) tracking of the mass media campaign, (3) penetration and reach of the IPC intervention, and (4) acceptability of the WC.

First, to monitor the availability and distribution of the WC, we will review monitoring data from SFH to track the availability of the WC throughout Lusaka. SFH is keeping track of distributions of the WC to determine how many WC products are purchased throughout the year. To assess availability to potential customers, we are implementing mystery shopper techniques to visit pharmacies and other distribution venues in all wards to determine if the WC is available and in stock. This can be cross-compared with records kept by the SFH of how many WCs have been purchased and distributed throughout Lusaka.

Second, we are working with SFH to ensure that all components of the mass media intervention are consistently rolled out, for example, checking that the website is up to date and the pages are successfully loading. The billboards are being checked periodically to ensure that they are still being viewed.

Third, we are working with SFH to randomly visit IPC recruitment and sessions. We are conducting “spot checks” and attending a random selection of IPC activities to determine if the IPC is being implemented and if the IPC agent is adhering to the training curriculum and key components of the intervention. We are also comparing logs with IPC agents regarding how many individuals attend the IPC. IPC agents are collecting ”client forms” during IPC sessions to provide information on the number of participants, date, location, and gender composition of the sessions. We have developed and implemented monitoring tools to collect information at the IPC sessions on participation, quality of delivery, and frequency of IPC sessions in each ward to measure the intervention intensity and penetration. The evaluation team is also monitoring the process of setting up IPC appointments and tracking (on random visits) how many invitations for IPC are sent out to measure take-up of the intervention. This is running parallel to the administrative/monitoring data that SFH is collecting.

Lastly, 30 qualitative focus group discussions are being conducted to understand how the WC product is being received in the communities. SFH may also collect short user surveys or collect qualitative data that can be shared. This will help determine if the product is available and if the mass media is being seen/accessed. It will also help us understand any reactions to the WC, how the messaging is being interpreted, and the acceptability of the new product to the community.

The evaluation team will work closely with the SFH team to ensure all administrative data needed for analysis are collected during the intervention. We will also note if any other major SRH activities are occurring throughout the study period, for example, any other products added to the market, any major stockouts of existing products, or any widespread education campaigns that might impact the IPC intervention. Overall this process evaluation will determine key factors that may impact the outcomes of the IPC intervention (i.e., availability of the WC, the consistency of the media campaign, and the quality of and reach of the IPC intervention). The process evaluation began when the project was rolled out, and is ongoing until the endline survey begins.

### Data management and analysis plan

The data are collected into an Android phone using SurveyCTO software; the data obtained are cleaned and exported into Stata for analysis. A high frequency check is run every two to three days to highlight any errors in data collection. Twenty percent of all participants (eligible or ineligible) are being randomly selected for back checking. The back check includes confirmation of ineligibility or administration of a 5- to 10-min version of the original survey to compare responses. All data are encrypted using Boxcryptor and stored on the SurveyCTO cloud and Box. A de-identified version of the data and statistical code will be shared on Dataverse at the completion of the study.

We will report the trial according to the CONSORT standards for reporting RCTs. This is a behavioral intervention unlikely to produce adverse effects, so analysis will be undertaken immediately once the endline survey has been completed. Baseline survey data will be analyzed to measure differences between the groups and between the wards at baseline. Randomization can be checked at this point. The main analysis will take place after endline data have been collected, to measure the impact of the introduction of the WC and the IPC intervention on condom use, controlling for any potential confounders or explanatory factors detected from the baseline analysis.

To assess the impact of the introduction of the new and premium WC on the Zambian condom market, the evaluation team will use the baseline survey as a quasi-control arm. While there are limitations with this approach, it will allow for measurement of changes in condom use, brand switching, user preferences, and uptake of the new product. The main limitation is that the study cannot determine attribution; however, given the challenges to create a better counterfactual, the evaluating and implementing teams agreed that this is the best approach in view of programmatic constraints.

The baseline survey will occurred at a time when there was no WC product available, no mass media, and no IPC. The study outcomes are self-reported condom (male or female) use ever, during the past 6 months, and at last sexual intercourse. The study will measure these indicators at baseline (no WC available) and endline (WC available). By analyzing changes in these indicators, the study will show changes in overall condom use as well as uptake of the WC in areas with only mass media versus mass media and IPC.

For the RCT component of the study, we will analyze the impact of the IPC intervention on our outcomes of interest (male condom use, WC use, willingness to use the WC), comparing intervention to control wards. Analyses will be conducted in Stata v12 (StataCorp, College Station, TX, USA). Results will be adjusted for any ward level clustering if it is identified. Multivariate regression analyses will be carried out to determine the impact of the IPC intervention on condom use (male condom and WC), controlling for demographic characteristics of participants.

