
### Sample size

To calculate the sample size needed in each trial arm, we considered prevalence of any condom use (percentage) as our outcome of interest. The contraceptive prevalence rate (CPR) for any modern contraceptive method in urban Zambia (for 15- to 49-year-old married women) is currently about 53% [4]. However, our study includes both married and unmarried women. A report from 2009 by the Zambian Statistics Office reported urban condom use to be 54% in Zambia [7]. We used 53% to calculate our sample size, and aim to detect a minimum increase of 5% use with 80% power at the 95% significance level. Because the trial is clustered at the ward level (with many individuals living within a ward), the sample size needs to be increased to account for intraclass correlation (ICC) within wards. However, no information was found from previous studies on the likely between- or within-cluster correlations in FC use in previous cluster-randomized trials. When the ICC cannot be estimated, common practice is to double the sample size to account for clustering.

Using Stata (StataCorp, College Station, TX, USA), we calculated the sample size required to detect a 4%, 5%, and 7% increase in any use from a 53% baseline use and an estimated standard deviation (SD) of 0.15, doubling the sample size to account for the unknown ICC. Lastly, we added 10% to increase the sample size to account for potential refusals. We will use a sample size of 1157 individuals per arm (a total of 2314 individuals in both arms). This yields a total of 58 individuals to be interviewed per ward, in a total of 40 wards (see Table 2).

**Table 2 Tab2:** Sample size required to detect a 2, 3, and 4 percentage point increase in condom use (4%, 5%, and 7% increase)

Hypothesized standard deviation of condom use	Hypothesized increase in proportion of condom use between groups	Sample size required in each group (ratio 1:1)	Adjusted for effect of clustering (design effect = 2)	10% refusal rate (estimated)
0.15	7%	296	592	651
0.15	5%	526	1052	1157
0.15	4%	1183	2366	2603

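### Wards are randomised, but the IPC comparison is adjusted for ward clustering only conditionally, so its confidence intervals can be too narrow

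*Protocol article*

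**What the plan says.** The ward is the unit of allocation. Under Methods/design, the forty wards "will be randomized to the control or intervention arm with a 1:1 allocation ratio". Survey and randomization confirms that "all 40 wards were randomized to receive the control (WC plus mass media) or intervention".

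Sample size accepts the consequence: "Because the trial is clustered at the ward level (with many individuals living within a ward), the sample size needs to be increased" to allow for intraclass correlation. No ICC was available, so the planners fell back on a convention: "When the ICC cannot be estimated, common practice is to double the sample size to account for clustering".

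The analysis text is weaker. In the paragraph on the RCT component, Data management and analysis plan states: "Results will be adjusted for any ward level clustering if it is identified". Statistical methods adds: "Multilevel models may be implemented to control for individual and ward level correlation, as individuals are nested within wards". The effect measures are odds ratios with 95% confidence intervals. No sentence commits those odds ratios to an analysis that always accounts for ward, and no sentence says how clustering would be identified.

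**The concern.** When whole wards are allocated, people in the same ward share both the allocation and whatever else makes the ward distinctive. The variance of the arm comparison then includes between-ward variation, whether or not a test detects it. An individual-level regression that omits ward leaves that component out, so its intervals are too short.

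Making the adjustment depend on detection has two weaknesses. First, with 40 wards a test for clustering has limited power at small ICCs, yet with 58 people per ward a small ICC still matters. Second, no criterion is fixed in advance, so whether to adjust could be decided after the endline data are seen, and separately for each of the several primary outcomes. What is at stake is the stated precision of the IPC effect and the rate of false-positive findings.

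**Working it through.** **Inputs from the protocol article.** 40 wards, 1:1, so 20 per arm; 1157 people per arm, 2314 in total; design effect 2; baseline condom use 53%. The article gives no ICC.

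**The plan's own figures.** Table 2 starts from 526 per arm. 526 × 2 = 1052; 1052 × 1.10 = 1157.2, stated as 1157; 2 × 1157 = 2314; 2314 / 40 = 57.85, stated as 58 per ward. The clustering and refusal steps reproduce. (Whether 526 follows from the stated power and SD is a separate question and does not affect this point.)

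**ICC implied by the plan.** Design effect = 1 + (m − 1) × ICC with m = 57.85. Setting it to 2 gives ICC = 1 / 56.85 = 0.0176.

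**If ward is never adjusted for.** The unadjusted standard error is too small by a factor √DE, so the true two-sided error of a nominal 5% test is 2 × [1 − Φ(1.96 / √DE)]. At DE = 2, √2 = 1.414 and 1.96 / 1.414 = 1.386. Type I error is then 0.166 and coverage 0.834, and the interval is 1 / 1.414 = 71% of its proper width.

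**If adjustment follows a test.** This was simulated with 20,000 null trials per ICC: beta-binomial outcomes, 20 wards per arm, 58 per ward, prevalence 0.53. The assumed criterion is a 5% test of ward heterogeneity. If it is positive, a ward-level t-test on 38 df is used; otherwise the unadjusted test is used. Where two values are shown, they come from separate runs and differ by simulation error or by the form of the pre-test.

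| ICC (assumed) | Design effect | Clustering missed | Type I error, overall | Type I error where missed | Type I error, never adjusted |
|---|---|---|---|---|---|
| 0.005 | 1.28 | 67–68% | 6.6–6.8% | about 9% | 8.4% |
| 0.01 | 1.57 | 33–34% | 6.3% | about 12% | 11.8% |
| 0.0176 | 2.00 | about 8% | 5.4–5.5% | 16–18% | 16.6% |
| 0.03 | 2.71 | 0.4% | 5.1% | too few to matter | 23.3% |
| 0.05 | 3.84 | about 0% | 4.9–5.0% | none to speak of | 31.7% |

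**If the criterion is an estimated ICC above zero.** Under the same set-up, overall type I error is 4.8%, 5.0% and 5.1% at ICC 0.005, 0.01 and 0.0176.

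**If ward is always adjusted for.** The ward-level t-test gives 4.7% to 5.3% at every ICC tried from 0 to 0.05.

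**The case against.** The strongest reply is that the article does promise adjustment where clustering is found, and substantial clustering would nearly always be found. At the planned design effect a 5% pre-test misses it in only about 8% of trials, and the overall error is about 5.4%. This stands. A reader might infer from the never-adjusted column that the trial will run at 16.6% or more, but the documents do not support that. Those figures describe an analysis that ignores ward altogether. The optional wording does not exclude that analysis, but the stated rule does not prescribe it.

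A reader might also say that the analysis contradicts the planned design effect. That goes too far. The sample was doubled because the ICC was unknown, and allowing for possible clustering while adjusting only when it is seen is an inconsistency of rigour, not a clash of figures.

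The multilevel sentence can be read as leaving the method open, which an analysis plan may properly settle, and the article also intends to calculate rates per ward. That sentence is therefore supporting evidence only. The case rests on the conditional one.

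Finally, a reader might extend the point to the baseline–endline comparison. The conditional sentence sits in the paragraph on the RCT component. Both surveys sample the same 40 wards, so stable ward effects largely cancel in that contrast and the figures above do not carry over.

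None of this supplies the missing commitment or criterion. Nor is the point merely a detail left to an analysis plan: the article states a rule, and the rule is unsuitable for a ward-randomised trial.

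**Conclusion.** The point holds for the IPC-versus-control comparisons. Conditional adjustment is inconsistent with ward randomisation and can give intervals that are too narrow.

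The average harm is modest under a consistently applied rule: overall type I error of about 5% to 6.8% with a 5% pre-test, and about 5% if any positive ICC estimate triggers adjustment. The harm is larger in the particular trials where clustering goes undetected, and largest if the option to adjust is not taken up at all. The ICC range and both criteria are assumptions, because the article gives neither. The simulations use a prevalence of 53%, so they describe any-condom use rather than use of the Woman's Condom.

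The case for changing the text rests mainly on the design principle and on the undefined criterion, not on a large expected inflation.

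**What to change.** In Data management and analysis plan, delete the closing condition from the sentence on ward clustering. In Statistical methods, replace the optional wording on multilevel models with a commitment. For example: *Every comparison of IPC with control will account for ward as the unit of randomisation, whatever the observed intraclass correlation.*

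Name one method for the primary analysis: a logistic model with a ward random effect; GEE or cluster-robust standard errors with a small-sample correction for 40 wards; or an analysis of ward summaries. Make the change before endline data are examined.

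The cost is two sentences and no extra data. Intervals will be somewhat wider: about 1.41 times the unadjusted width at a design effect of 2, and little changed if the ICC is near zero. The sample was already doubled with that loss of precision in mind.
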